### Subgroup analyses

Subgroup analyses will be performed with mixed effects Cox proportional hazard models for the primary outcome. We intend to report interaction p-values and hazard ratios of Plasma-Lyte against Saline and Slow against Rapid infusion in each subgroup:

Patients with and without sepsis, defined using Sepsis 3 criteria.^(2)^Patients with baseline KDIGO 1 and those ≥ 2.Surgical and nonsurgical patients.Patients with or without traumatic brain injury.Patients with Acute Physiology and Chronic Health Evaluation II (APACHE II)^(12)^ ≥ 25 and < 25 points.Patients who received > 1.000mL *versus* ≤ 1.000mL in the 24 hours before randomization.

### Sensitivity analyses

A per protocol analysis for the primary outcome will also be carried out as a sensitivity analysis, accounting for adherence to the allocated solution and infusion speed. As the per protocol population, we will consider patients meeting all inclusion and exclusion criteria that were infused in at least one allocated group (A to F) a solution bolus at the allocated speed on the first day after randomization. We plan a sensitivity analysis for KDIGO criteria considering only creatinine levels for categorization.

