**Figure 2 f2:**
[figure not shown]
Infusion speed.

Blinding to fluid type was possible due to identical bags manufactured by Baxter LA® labeled “A” to “F” (six types, with half of the letters saline and half Plasma-Lyte 148). Sites were instructed to use the study fluid for the fluid challenge, maintenance and, whenever possible, for the dilution of all drugs (if compatible) that required an infusion volume over 100mL. Use of fluid bolus and fluid management was left to the discretion of the attending physician due to the pragmatic nature of the trial; however, guidelines and good-clinical practices in fluid management were provided to the sites in the study material and were discussed during the investigator´s meetings. Infusion speed could not be blinded.

The answers to these two questions are important because it is presently unclear whether balanced (low chloride) solutions are beneficial for critically ill patients and because no large clinical trial has ever assessed the effects of varying infusion speeds on robust patient-centered outcomes.

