### Planned statistical analysis for the primary, secondary and tertiary endpoints

All clinical endpoints shall be presented as similar as possible to those shown in table 2. Categorical variables will be presented as the number and percentage. Continuous variables will be presented as the mean and standard deviation for variables such as age and physiological parameters (blood pressure, sodium and potassium levels). We will favor the presentation of ordinal variables, such as Sequential Organ Failure Assessment (SOFA) score, as the median and interquartile range. An alpha of 5% and 95% confidence intervals will be used unless otherwise stated; similarly, all analyses will be based on the intention-to-treat principle unless otherwise stated. Analyses will be performed with the latest R version available at the end of the patients’ follow-up (most probably version 4.0).

**Table 2 t2:** Outcomes comparing slow versus fast infusion speed and Plasma-Lyte versus 0.9% sodium chloride

Characteristics	Plasma-Lyte	0.9% Sodium chloride	Effect measure	p value*	Slow infusion	Rapid infusion	Effect measure	p value†	p value‡
			(95%CI)		(n = xxx)	(n = xxx)	(95%CI)		
Primary outcome									
90-day mortality	xx.x (xx.x)	xx.x (xx.x)	x.xx (x.xx - x.xx)	x.xx	xx.x (xx.x)	xx.x (xx.x)	x.xx (x.xx - x.xx)	x.xx	x.xx
Secondary outcomes									
Acute renal failure with need for renal replacement therapy within 90 days									
Incidence (per 1000 patient-day)	xx.x	xx.x	x.xx (x.xx - x.xx)	x.xx	xx.x	xx.x	x.xx (x.xx - x.xx)	x.xx	x.xx
At day 1	xx.x (xx.x)	xx.x (xx.x)		-	xx.x (xx.x)	xx.x (xx.x)		-	-
At day 2	xx.x (xx.x)	xx.x (xx.x)		-	xx.x (xx.x)	xx.x (xx.x)		-	-
At day 3	xx.x (xx.x)	xx.x (xx.x)		-	xx.x (xx.x)	xx.x (xx.x)		-	-
At day 7	xx.x (xx.x)	xx.x (xx.x)		-	xx.x (xx.x)	xx.x (xx.x)		-	-
In hospital (at least one renal substitution in hospital stay)	xx.x (xx.x)	xx.x (xx.x)	x.xx (x.xx - x.xx)	x.xx	xx.x (xx.x)	xx.x (xx.x)	x.xx (x.xx - x.xx)	x.xx	x.xx
Unknown at 90-day follow up	xx.x (xx.x)	xx.x (xx.x)		-	xx.x (xx.x)	xx.x (xx.x)		-	-
Lost contact for 90-day follow-up	xx.x (xx.x)	xx.x (xx.x)		-	xx.x (xx.x)	xx.x (xx.x)		-	-
Incident renal failure (using KDIGO ≥ 2) at day 3	xx.x (xx.x)	xx.x (xx.x)	x.xx (x.xx - x.xx)	x.xx	xx.x (xx.x)	xx.x (xx.x)	x.xx (x.xx - x.xx)	x.xx	x.xx
KDIGO ≥ 2 or death at day 3	xx.x (xx.x)	xx.x (xx.x)	x.xx (x.xx - x.xx)	x.xx	xx.x (xx.x)	xx.x (xx.x)	x.xx (x.xx - x.xx)	x.xx	x.xx

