### Protocol adherence

Protocol compliance will be described as presented in tables 3 and 4, reporting the volume of fluids infused on days 1, 2, 3 and 7 comparing Plasma-Lyte 148 or 0.9% saline and the proportion of expansion fluids in the randomized infusion speed (slow or rapid). For the purpose of reporting, any fluid challenge at the incorrect speed will be considered a protocol deviation. The use of normal saline, Lactated Ringer, or other crystalloids above 100mL^(1)^ for diluents or a bolus will also be reported as deviations in the tables.

**Table 3 t3:** Adherence to protocol (for the Plasma-Lyte *versus* 0.9% sodium chloride)3

	Plasma-Lyte		0.9% Sodium chloride		p value
	Patients	Volume received - mL	Patients	Volume received - mL	
Trial fluid					
Day 1	xx (xx.x)	xxxx [xxxx - xxxx]	xx (xx.x)	xxxx [xxxx - xxxx]	x.xx
Day 2	xx (xx.x)	xxxx [xxxx - xxxx]	xx (xx.x)	xxxx [xxxx - xxxx]	x.xx
Day 3	xx (xx.x)	xxxx [xxxx - xxxx]	xx (xx.x)	xxxx [xxxx - xxxx]	x.xx
Day 7	xx (xx.x)	xxxx [xxxx - xxxx]	xx (xx.x)	xxxx [xxxx - xxxx]	x.xx
Open label 0.9% sodium chloride					
Day 1	xx (xx.x)	xxxx [xxxx - xxxx]	xx (xx.x)	xxxx [xxxx - xxxx]	x.xx
Day 2	xx (xx.x)	xxxx [xxxx - xxxx]	xx (xx.x)	xxxx [xxxx - xxxx]	x.xx
Day 3	xx (xx.x)	xxxx [xxxx - xxxx]	xx (xx.x)	xxxx [xxxx - xxxx]	x.xx
Day 7	xx (xx.x)	xxxx [xxxx - xxxx]	xx (xx.x)	xxxx [xxxx - xxxx]	x.xx
Open Label Plasma-Lyte					
Day 1	xx (xx.x)	xxxx [xxxx - xxxx]	xx (xx.x)	xxxx [xxxx - xxxx]	x.xx
Day 2	xx (xx.x)	xxxx [xxxx - xxxx]	xx (xx.x)	xxxx [xxxx - xxxx]	x.xx
Day 3	xx (xx.x)	xxxx [xxxx - xxxx]	xx (xx.x)	xxxx [xxxx - xxxx]	x.xx
Day 7	xx (xx.x)	xxxx [xxxx - xxxx]	xx (xx.x)	xxxx [xxxx - xxxx]	x.xx
Other nontrial crystalloids					
Day 1	xx (xx.x)	xxxx [xxxx - xxxx]	xx (xx.x)	xxxx [xxxx - xxxx]	x.xx
Day 2	xx (xx.x)	xxxx [xxxx - xxxx]	xx (xx.x)	xxxx [xxxx - xxxx]	x.xx
Day 3	xx (xx.x)	xxxx [xxxx - xxxx]	xx (xx.x)	xxxx [xxxx - xxxx]	x.xx
Day 7	xx (xx.x)	xxxx [xxxx - xxxx]	xx (xx.x)	xxxx [xxxx - xxxx]	x.xx
Other nontrial colloids					
Day 1	xx (xx.x)	xxxx [xxxx - xxxx]	xx (xx.x)	xxxx [xxxx - xxxx]	x.xx
Day 2	xx (xx.x)	xxxx [xxxx - xxxx]	xx (xx.x)	xxxx [xxxx - xxxx]	x.xx
Day 3	xx (xx.x)	xxxx [xxxx - xxxx]	xx (xx.x)	xxxx [xxxx - xxxx]	x.xx
Day 7	xx (xx.x)	xxxx [xxxx - xxxx]	xx (xx.x)	xxxx [xxxx - xxxx]	x.xx
Packed red blood cells					
Day 1	xx (xx.x)	xxxx [xxxx - xxxx]	xx (xx.x)	xxxx [xxxx - xxxx]	x.xx
Day 2	xx (xx.x)	xxxx [xxxx - xxxx]	xx (xx.x)	xxxx [xxxx - xxxx]	x.xx

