Day 3	xx (xx.x)	xxxx [xxxx - xxxx]	xx (xx.x)	xxxx [xxxx - xxxx]	x.xx
Day 7	xx (xx.x)	xxxx [xxxx - xxxx]	xx (xx.x)	xxxx [xxxx - xxxx]	x.xx

Results expressed as n (%) or median [interquartile range].

**Table 4 t4:** Adherence to the protocol (for the slow versus fast infusion speed comparison)

Speed adherence	Slow infusion speed group	Fast infusion speed group	p value
Day 1			
Patient with at least one bolus infused for expansion	xx/xx (xx.x)	xx/xx (xx.x)	x.xx
All fluid challenges at the allocated speed	xx/xx (xx.x)	xx/xx (xx.x)	x.xx
Maintenance fluid	xx/xx (xx.x)	xx/xx (xx.x)	x.xx
Other infusion	xx/xx (xx.x)	xx/xx (xx.x)	x.xx
Day 2			
Patient with at least one bolus infused for expansion	xx/xx (xx.x)	xx/xx (xx.x)	x.xx
All fluid challenges at the allocated speed	xx/xx (xx.x)	xx/xx (xx.x)	x.xx
Maintenance fluid	xx/xx (xx.x)	xx/xx (xx.x)	x.xx
Other infusion	xx/xx (xx.x)	xx/xx (xx.x)	x.xx
Day 3			
Patient with at least one bolus infused for expansion	xx/xx (xx.x)	xx/xx (xx.x)	x.xx
All fluid challenges at the allocated speed	xx/xx (xx.x)	xx/xx (xx.x)	x.xx
Maintenance fluid	xx/xx (xx.x)	xx/xx (xx.x)	x.xx
Other infusion	xx/xx (xx.x)	xx/xx (xx.x)	x.xx
Day 7			
Patient with at least one bolus infused for expansion	xx/xx (xx.x)	xx/xx (xx.x)	x.xx
All fluid challenges at the allocated speed	xx/xx (xx.x)	xx/xx (xx.x)	x.xx
Maintenance fluid	xx/xx (xx.x)	xx/xx (xx.x)	x.xx
Other infusion	xx/xx (xx.x)	xx/xx (xx.x)	x.xx

Results expressed as n (%).

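### The single per-protocol set, entered by one correct day-1 bolus, only weakly accounts for adherence and should be defined separately for fluid and for speed

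*SAP article*

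**What the plan says.** Under Planned statistical analysis, the default population is intention-to-treat: "all analyses will be based on the intention-to-treat principle unless otherwise stated". Under Sensitivity analyses, the plan adds a per-protocol analysis of the primary outcome, "accounting for adherence to the allocated solution and infusion speed". Patients must be eligible and have been "infused in at least one allocated group (A to F) a solution bolus at the allocated speed on the first day after randomization". The sentence is awkwardly built, but every reading sets a minimum of one correct bolus. No reading requires all boluses to be correct, and none limits non-trial fluid. Only one set is defined.

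Under Protocol adherence, the standard used for reporting is stricter. On speed, "any fluid challenge at the incorrect speed will be considered a protocol deviation". Non-trial crystalloid above 100 mL "for diluents or a bolus will also be reported as deviations in the tables". For days 1, 2, 3 and 7, Table 4 carries the row "All fluid challenges at the allocated speed", and Table 3 gives volumes of trial fluid, open-label saline, open-label Plasma-Lyte and other crystalloids.

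The text after Figure 2 makes the fluid allocation wider than boluses: "Sites were instructed to use the study fluid for the fluid challenge, maintenance and, whenever possible, for the dilution of all drugs", where compatible and above 100 mL. It also says: "Use of fluid bolus and fluid management was left to the discretion of the attending physician".

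**The concern.** This is the only analysis of the primary outcome that the plan describes as accounting for adherence. Two features limit how far it does so.

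First, the entry condition is a minimum exposure. After one qualifying bolus, nothing else on day 1 or later affects membership, whether further challenges at the wrong speed or large volumes of another crystalloid.

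Second, a joint condition on solution, bolus and speed is applied to two separate questions. Adherence to fluid can be complete in a patient who had no day-1 bolus, or whose boluses all ran at the wrong speed. That patient still leaves the fluid comparison.

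A per-protocol estimate close to the intention-to-treat one would then say little about whether imperfect adherence matters. In the fluid comparison, patients are lost for a reason unrelated to fluid.

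**Working it through.** **1. The plan's own figure.** Inputs from Sample size calculation: 11,000 patients, 35% control mortality, HR 0.9. From Planned statistical analysis: alpha 5%, taken as two-sided. With 1:1:1:1 allocation each margin is 5,500 versus 5,500.

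- Experimental risk under proportional hazards: 1 − 0.65^0.9 = 0.3214.
- Events: 5,500 × (0.35 + 0.3214) = 3,693.
- Schoenfeld power: Φ(√3,693/2 × |ln 0.9| − 1.96) = Φ(3.20 − 1.96) = 89.3%.

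The stated 89% reproduces. It belongs to the intention-to-treat analysis; the plan gives no figure for the per-protocol set.

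**2. The rules side by side.**

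| Eligible patient | Planned per-protocol set | Protocol adherence section |
|---|---|---|
| One correct day-1 bolus, then wrong-speed challenges | In, both comparisons | Speed deviation |
| One correct day-1 bolus, plus over 100 mL of a non-trial crystalloid as bolus or diluent | In, both comparisons | Fluid deviation |
| Allocated fluid only, all day-1 boluses at the wrong speed | Out of both | Speed deviation, no fluid deviation |
| Allocated fluid only, as maintenance or diluent, no day-1 bolus | Out of both | No deviation |

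The first two rows show weak accounting for adherence. The last two show fluid-adherent patients lost from the fluid comparison.

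**3. How far apart one correct bolus and all correct can be.** The plan gives neither adherence nor bolus counts, so these are assumptions: k day-1 boluses per patient, each at the allocated speed with probability q, independently.

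- At least one correct: 1 − (1 − q)^k.
- All correct: q^k.
- Share of the planned set with a speed deviation: 1 − q^k / [1 − (1 − q)^k].

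| q | k | At least one correct | All correct | Share with a deviation |
|---|---|---|---|---|
| any of 0.5 to 0.9 | 1 | q | q | 0% |
| 0.9 | 2 | 99.0% | 81.0% | 18% |
| 0.8 | 3 | 99.2% | 51.2% | 48% |
| 0.7 | 3 | 97.3% | 34.3% | 65% |

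The gap depends on how many boluses patients received, which was left to the physician.

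**4. What this could do to a hazard ratio.** Suppose a fraction d of the set deviates and gets no effect at all. A true HR of 0.90 then appears as exp[(1 − d) ln 0.9]: 0.910, 0.919 and 0.929 for d = 0.1, 0.2 and 0.3. On the log scale the shifts are 0.011, 0.021 and 0.032. Even with all 3,693 events the standard error is about 2/√3,693 = 0.033, so the shifts are roughly 0.3 to 1 standard error. Neither d nor the zero effect comes from the plan.

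**5. Precision of a stricter set.** If it keeps 70% or 50% of the events (2,585 or 1,846), power at HR 0.9 is Φ(√2,585/2 × 0.1054 − 1.96) = 76% or Φ(√1,846/2 × 0.1054 − 1.96) = 62%.

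**The case against.** The strongest defence is that the two sections do different jobs. The speed rule under Protocol adherence is expressly for reporting and governs descriptive tables; a reportable deviation need not remove a patient from an analysis set. That stands. A reader might infer that the plan contradicts itself, but it does not. The point is only that the set falls short of its own description.

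A minimum-exposure rule also has merit. Requiring every challenge to be correct becomes harder with each bolus, so it selects on bolus count, plausibly a marker of severity, and may discard much of the sample (step 3). That stands too, and is why a stricter set should sit beside a lenient one and not replace it.

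A reader might also infer that open-label speed carries selection bias into the fluid comparison. The documents give little support for this. Fluid type is blinded and allocation is factorial, so the choice of speed should not depend on knowing the fluid arm, and losses for speed should be similar in both. The demonstrable cost is patients and generalisability.

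Finally, not all non-trial fluid is contamination. Study fluid as diluent was asked for only where possible and compatible, and open-label saline in the saline arm is the allocated fluid. A strict rule that ignores this would exclude patients managed as instructed. Open-label fluid also enters the planned chloride-load analysis, though only as exploratory work.

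None of this answers the use of one joint set for two questions. The inclusion criteria require a need for fluid resuscitation, so patients without a day-1 bolus may be few, but the plan gives no count.

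**Conclusion.** The point holds in a limited form. The single per-protocol set accounts only weakly for adherence to solution and speed, and it removes fluid-adherent patients from the fluid comparison for reasons of speed or bolus timing. Both follow from the text without any assumption.

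The size does not. The 18% to 65% range rests on assumed adherence, bolus counts and independence, and falls to zero at one bolus per patient. A reader might take the hazard ratios of 0.91 to 0.93 as the expected dilution, or conclude that the analysis is useless. Neither is supported: those ratios assume a deviation rate and no effect in partly exposed patients, and the set does remove ineligible patients and those with no correct day-1 bolus. No comparison with the dilution in the intention-to-treat analysis can be made.

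This concerns one sensitivity analysis. The intention-to-treat primary analysis and its 89% power are unaffected. The change is worth making before the allocation is known to the analysts, because afterwards the choice of set could follow the results.

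**What to change.** Replace the joint definition with one per-protocol set per comparison, and add a stricter supportive set for each:

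- **Fluid, per-protocol:** eligible and received the allocated trial fluid on day 1, whatever the speed.
- **Fluid, stricter:** in addition, no crystalloid of the opposite or another type above the 100 mL reporting limit on day 1. Do not count open-label saline in the saline arm, or diluents where trial fluid was incompatible.
- **Speed, per-protocol:** eligible and received at least one day-1 challenge at the allocated speed.
- **Speed, stricter:** in addition, all day-1 challenges at the allocated speed.

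Use the primary model's covariates. State that deviations after day 1 remain in all four sets, and label the results non-randomised because they condition on post-randomisation events. Report the number excluded by arm and by reason. This matters most for the stricter fluid set, where open-label saline excludes patients in one arm only.

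The cost is SAP wording and a few extra model fits. Tables 3 and 4 already call for most of the data; they do not show whether diluent incompatibility was recorded, so the plan should say how that exemption is applied. The stricter sets will be smaller, with the loss of precision shown in step 5, and will partly select on number of boluses, so they should be read only as support.

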### Protocol adherence

Protocol compliance will be described as presented in tables 3 and 4, reporting the volume of fluids infused on days 1, 2, 3 and 7 comparing Plasma-Lyte 148 or 0.9% saline and the proportion of expansion fluids in the randomized infusion speed (slow or rapid). For the purpose of reporting, any fluid challenge at the incorrect speed will be considered a protocol deviation. The use of normal saline, Lactated Ringer, or other crystalloids above 100mL^(1)^ for diluents or a bolus will also be reported as deviations in the tables.

**Table 3 t3:** Adherence to protocol (for the Plasma-Lyte *versus* 0.9% sodium chloride)3

	Plasma-Lyte		0.9% Sodium chloride		p value
	Patients	Volume received - mL	Patients	Volume received - mL	
Trial fluid					
Day 1	xx (xx.x)	xxxx [xxxx - xxxx]	xx (xx.x)	xxxx [xxxx - xxxx]	x.xx
Day 2	xx (xx.x)	xxxx [xxxx - xxxx]	xx (xx.x)	xxxx [xxxx - xxxx]	x.xx
Day 3	xx (xx.x)	xxxx [xxxx - xxxx]	xx (xx.x)	xxxx [xxxx - xxxx]	x.xx
Day 7	xx (xx.x)	xxxx [xxxx - xxxx]	xx (xx.x)	xxxx [xxxx - xxxx]	x.xx
Open label 0.9% sodium chloride					
Day 1	xx (xx.x)	xxxx [xxxx - xxxx]	xx (xx.x)	xxxx [xxxx - xxxx]	x.xx
Day 2	xx (xx.x)	xxxx [xxxx - xxxx]	xx (xx.x)	xxxx [xxxx - xxxx]	x.xx
Day 3	xx (xx.x)	xxxx [xxxx - xxxx]	xx (xx.x)	xxxx [xxxx - xxxx]	x.xx
Day 7	xx (xx.x)	xxxx [xxxx - xxxx]	xx (xx.x)	xxxx [xxxx - xxxx]	x.xx
Open Label Plasma-Lyte					
Day 1	xx (xx.x)	xxxx [xxxx - xxxx]	xx (xx.x)	xxxx [xxxx - xxxx]	x.xx
Day 2	xx (xx.x)	xxxx [xxxx - xxxx]	xx (xx.x)	xxxx [xxxx - xxxx]	x.xx
Day 3	xx (xx.x)	xxxx [xxxx - xxxx]	xx (xx.x)	xxxx [xxxx - xxxx]	x.xx
Day 7	xx (xx.x)	xxxx [xxxx - xxxx]	xx (xx.x)	xxxx [xxxx - xxxx]	x.xx
Other nontrial crystalloids					
Day 1	xx (xx.x)	xxxx [xxxx - xxxx]	xx (xx.x)	xxxx [xxxx - xxxx]	x.xx
Day 2	xx (xx.x)	xxxx [xxxx - xxxx]	xx (xx.x)	xxxx [xxxx - xxxx]	x.xx
Day 3	xx (xx.x)	xxxx [xxxx - xxxx]	xx (xx.x)	xxxx [xxxx - xxxx]	x.xx
Day 7	xx (xx.x)	xxxx [xxxx - xxxx]	xx (xx.x)	xxxx [xxxx - xxxx]	x.xx
Other nontrial colloids					
Day 1	xx (xx.x)	xxxx [xxxx - xxxx]	xx (xx.x)	xxxx [xxxx - xxxx]	x.xx
Day 2	xx (xx.x)	xxxx [xxxx - xxxx]	xx (xx.x)	xxxx [xxxx - xxxx]	x.xx
Day 3	xx (xx.x)	xxxx [xxxx - xxxx]	xx (xx.x)	xxxx [xxxx - xxxx]	x.xx
Day 7	xx (xx.x)	xxxx [xxxx - xxxx]	xx (xx.x)	xxxx [xxxx - xxxx]	x.xx
Packed red blood cells					
Day 1	xx (xx.x)	xxxx [xxxx - xxxx]	xx (xx.x)	xxxx [xxxx - xxxx]	x.xx
Day 2	xx (xx.x)	xxxx [xxxx - xxxx]	xx (xx.x)	xxxx [xxxx - xxxx]	x.xx
Day 3	xx (xx.x)	xxxx [xxxx - xxxx]	xx (xx.x)	xxxx [xxxx - xxxx]	x.xx
Day 7	xx (xx.x)	xxxx [xxxx - xxxx]	xx (xx.x)	xxxx [xxxx - xxxx]	x.xx

Results expressed as n (%) or median [interquartile range].

**Table 4 t4:** Adherence to the protocol (for the slow versus fast infusion speed comparison)

Speed adherence	Slow infusion speed group	Fast infusion speed group	p value
Day 1			
Patient with at least one bolus infused for expansion	xx/xx (xx.x)	xx/xx (xx.x)	x.xx
All fluid challenges at the allocated speed	xx/xx (xx.x)	xx/xx (xx.x)	x.xx
Maintenance fluid	xx/xx (xx.x)	xx/xx (xx.x)	x.xx
Other infusion	xx/xx (xx.x)	xx/xx (xx.x)	x.xx
Day 2			
Patient with at least one bolus infused for expansion	xx/xx (xx.x)	xx/xx (xx.x)	x.xx
All fluid challenges at the allocated speed	xx/xx (xx.x)	xx/xx (xx.x)	x.xx
Maintenance fluid	xx/xx (xx.x)	xx/xx (xx.x)	x.xx
Other infusion	xx/xx (xx.x)	xx/xx (xx.x)	x.xx
Day 3			
Patient with at least one bolus infused for expansion	xx/xx (xx.x)	xx/xx (xx.x)	x.xx
All fluid challenges at the allocated speed	xx/xx (xx.x)	xx/xx (xx.x)	x.xx
Maintenance fluid	xx/xx (xx.x)	xx/xx (xx.x)	x.xx
Other infusion	xx/xx (xx.x)	xx/xx (xx.x)	x.xx
Day 7			
Patient with at least one bolus infused for expansion	xx/xx (xx.x)	xx/xx (xx.x)	x.xx
All fluid challenges at the allocated speed	xx/xx (xx.x)	xx/xx (xx.x)	x.xx
Maintenance fluid	xx/xx (xx.x)	xx/xx (xx.x)	x.xx
Other infusion	xx/xx (xx.x)	xx/xx (xx.x)	x.xx

Results expressed as n (%).

### Adverse events report

BaSICS will collect only Suspected Unexpected Serious Adverse Reaction (SUSAR) data from the sites.^(1)^ This information will be reported as the number of events per group for both interventions and for the possible four combinations in the study.

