**Results:**

BaSICS will have 90-day mortality as its primary endpoint, which will be tested using mixed-effects Cox proportional hazard models, considering sites as a random variable (frailty models) adjusted for age, organ dysfunction and admission type. Important secondary endpoints include renal replacement therapy up to 90 days, acute renal failure, organ dysfunction at days 3 and 7, and mechanical ventilation-free days within 28 days.

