**Serious Adverse Events**

Serious adverse events which are study related according to the site investigators should be urgently reported (within 24 hours from the onset of the event) to the coordinating centre. Those events will be immediately forwarded to the DMC members. A serious adverse event directly related to the study is defined as any event meeting the two following criteria:

1. Any fatal or life-threatening event (immediate risk of death), or any event that causes sequelae or permanent disability, or that extends hospitalization; AND
2. The primary physician believes that the event is related to the patient’s inclusion in the BaSICS study. Serious adverse events will be considered as “related to the study” if the primary physician believes that the event was probably caused by the fluid and/or rate of infusion used in the study and follows a plausible time sequence after the administration of the fluid.

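### The SAP collects and tabulates only SUSARs, but the DMC charter has sites report related serious events whether or not they are unexpected; one definition is needed for the adverse event table

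*SAP article*

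**What the plan says.** The SAP article addresses serious adverse events in two places.

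- **Adverse events report (main text).** "BaSICS will collect only Suspected Unexpected Serious Adverse Reaction (SUSAR) data from the sites". The next sentence fixes the output: "This information will be reported as the number of events per group for both interventions and for the possible four combinations in the study". The collection statement cites the protocol paper. It does not define *suspected* or *unexpected* and gives no list of expected reactions.
- **Appendix 1, DMC charter, Serious Adverse Events.** "Serious adverse events which are study related according to the site investigators should be urgently reported" to the coordinating centre within 24 hours, and "Those events will be immediately forwarded to the DMC members". Such an event must meet two criteria. The first is seriousness: "Any fatal or life-threatening event (immediate risk of death), or any event that causes sequelae or permanent disability, or that extends hospitalization; AND" The second is relation to the study, which holds if "the primary physician believes that the event was probably caused by the fluid and/or rate of infusion used in the study" and the timing is plausible. Neither criterion asks whether the event was expected.

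**The concern.** A SUSAR has to be serious, suspected of being a reaction, and unexpected. The charter's event has to be serious and probably caused by the fluid or the rate. An event that is serious, related and expected is therefore reportable under the charter, yet lies outside what the main text says is collected.

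What is at stake is the content and labelling of the adverse event table. The DMC would receive a class of attributed events that the table omits. Because the SAP does not say which reactions count as expected, someone would also have to sort events into expected and unexpected under a rule this document does not supply. The article says the plan exists to prevent bias from choices made once results are known, so the rule should be settled, or its source named, before database lock.

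**Working it through.** The documents state no adverse event figure, so there is nothing to recompute. The check is a comparison of the two rules.

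**Inputs**

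1. Main text, Adverse events report: serious, suspected, unexpected; *only* makes the list exclusive.
2. Appendix 1, Serious Adverse Events: serious and probably caused by fluid and/or rate; no expectedness test.
3. Assumptions: seriousness means the same in both places, and *suspected* is a lower bar than *probably caused*. The document defines neither point for SUSARs.

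**Cross-classification of serious events**

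| Causality | Expectedness | Reported to coordinating centre and DMC under the charter | Collected and tabulated under the main text |
|---|---|---|---|
| Probably caused | Unexpected | Yes | Yes |
| Probably caused | Expected | Yes | **No** |
| Suspected, short of probable | Unexpected | **No** | Yes |
| Suspected, short of probable | Expected | No | No |

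The rules agree in the first and last rows and disagree in the two middle rows. The second row is the gap at issue: expected, related serious reactions reach the DMC but not the table. The third row shows that the disagreement also runs the other way, so under these assumptions the two classes overlap and neither contains the other.

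**Is the second row reported anywhere else by arm?** Not as attributed events; no other section or table shell counts them. Part of the same harm is captured as outcomes, however. "BaSICS will have 90-day mortality as its primary endpoint", and Table 2 also compares, for both interventions, renal replacement therapy, KDIGO stage 2 or above at days 3 and 7 (alone and combined with death), four SOFA organ components and total SOFA, ventilation-free days within 28 days, ICU and hospital death, and lengths of stay. None of these depends on attribution or expectedness. What remains uncounted is expected, attributed serious reactions that do not show in those endpoints.

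**The case against.** The strongest reply has four parts.

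- **SUSAR may be loose wording.** The sentence cites the protocol paper, which is not at hand. If the authors meant the charter's related serious events, no data are lost. This may be so, but the term would then be wrong in the published plan, and readers would take the table to show unexpected events only. The contradiction lies within this one document and does not depend on the missing source.
- **Harm and cost may rest on opposite readings.** If sites really supply only SUSARs, a wording change cannot produce expected events; if the charter describes practice, they are already in hand. This stands. The document does not settle which holds, and the cost of the fix depends on it.
- **Much serious harm is compared anyway.** This stands and limits the point. A reader might infer that expected serious harms vanish from the published safety result; the endpoint list does not support that.
- **The charter is not simply the wider class.** This also stands. A reader might infer that SUSARs are a subset of the charter's events, so that a table built on the charter's definition alone would suffice. The charter's causality test may be stricter than *suspected*, and such a table could drop some SUSARs.

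**Conclusion.** The inconsistency is real and should be corrected. As written, the main text and the charter define different sets of serious events, and expected related serious reactions sent to the DMC would be absent from the published adverse event table.

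Its reach is limited. No estimate, test or primary conclusion changes. The charter's formal safety boundary uses the 90-day death rate (two-sided P below 0.01), not serious event counts. The major clinical outcomes are compared by arm regardless.

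The size is unknown. A reader might infer that most related events would be lost, or that particular reactions such as fluid overload or electrolyte disturbance are the ones excluded. The documents give no counts and do not list which reactions are expected, so neither inference is supported.

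The conclusion rests on reading SUSAR by its ordinary components and taking *only* at face value. If the term was used loosely, what remains is an error of wording.

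**What to change.** 1. Reconcile Adverse events report with the charter's Serious Adverse Events section by stating one definition of the events collected from sites, including the causality threshold and the source of the expected/unexpected classification.
2. In Adverse events report, tabulate for each comparison and for the four combinations all serious events reported to the coordinating centre as study related under the charter, together with any SUSARs that do not meet its *probably caused* test. Mark each as expected or unexpected.
3. If SUSAR was meant to denote the charter's events, replace the term.

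**Cost.** If the charter was followed, the reports already reach the coordinating centre, and the change is SAP wording, one table shell and the classification of events. The article says the plan was written before follow-up ended, so this could be done before database lock. If sites in fact supplied only SUSARs, the expected events cannot be recovered by rewording; the report should then say so, and the charter's description should be corrected to match.
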